*** This criterium might by subject to potential changes and might be further adapted according to (a) the current epidemiological situation, (b) the requirements of the Robert-Koch-Institute (RKI), (c) the test strategy as well as (d) the test capacity.

**Risk factors following the definition by the RKI, with own additions:
Diabetes mellitus (Types I and II)Cardiovascular disease (arterial hypertension, coronary heart disease, heart failure, other such as atrial fibrillation, peripheral artery disease, condition after apoplexy)Pulmonary disease (COPD, bronchial asthma, other)chronical nephrological diseasechronical hepatic disease such as liver cirrhosisimmunodeficiency due to underlying disease (malignant primary hematological disease (e.g. leukemia/ lymphoma), leukocytopenia, condition after organ or stem cell transplantation or potentially immunosuppressive medication intake such as glucocorticoids, immunosuppressive drugs, immunomodulators, cytostaticsactive oncological disease with immunodeficiency (excluding for example localized skin cancer such as squamous cell carcinoma or basal cell carcinoma)obesity (body mass index > 35)active smokingDown syndrome

All patients have to be 18 years and older, insured with the AOK Baden-Württemberg, participate in GP-based care, and have written and spoken German language skills.

If patients are unable to give their informed consent into study participation, a legal representative of the patient has to give their informed consent for study participation of the patient.

Participants for the process evaluation have to participate in the CovidCare study as either patient or health care provider, are 18 years and older, have written and spoken German language skills and have to be able to give their informed consent.

No further exclusion criteria have been defined.

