### Intervention description

Measures within the CovidCare-module include patient intake, an initial assessment and several telephone monitoring calls. In the initial assessment, information on risks (age, obesity, nicotine consumption, diabetes, cardiovascular disease, pulmonary disease, chronical hepatic disease, chronical nephrological disease, immunodeficiency, treatment of oncological disease with immunodeficiency, vaccination status), gender, SARS-CoV-2 status, living condition and SARS-CoV-2 status of contact persons, symptom history, legal information (health authorisation, patient decree) is collected and inclusion in the telephone monitoring is defined. The GP individually sets the presumable date of onset of COVID-19 and the extent and frequency of the telephone monitoring. GP-ascertained begin of COVID-19 equals to day 1. GPs are responsible to consider the appropriate monitoring intervals referring to the actual clinical knowledge base regarding the disease course with milestones for deterioration and recovery.

Patients are provided with a monitoring protocol that can be individualized, e.g. for daily log of symptoms and vital signs. The telephone monitoring includes a monitoring of symptoms and signs of infection and the cardio-respiratory system. Individual timelines and figures are created and provide an overview on first symptoms (presumable disease onset), positive test result, disease progression. This aids in assessing the state of health and early detection of a deterioration. A total number of at least three to four contacts is recommended, including the intake, the initial assessment and a closing contact. Any further contacts should be conducted in the critical phase as defined by the knowledge base provided by the RKI [12, 13], the frequency is to be increased with a deterioration. The closing contact includes a short closing documentation not later than three weeks after disease onset. In this closing contact, information on the utilisation of different health care services (e.g. hospitalisation, ventilation) are retrieved and documented.

No further telephone monitorings are conducted when (a) the patient is cured (defined as alive and without symptoms of COVID-19 for 48 h and longer), (b) the patient is hospitalised, (c) the patient has passed away, (d) none of the above has happened not later than three weeks after first symptoms showed.

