### Participant timeline

Development of study material, such as assessments, and software programming has started in March 2020. The CovidCare-module is available for eligible general practices since April 30th 2020. Patient recruitment for this study in the general practices can start as soon as the software has been installed and activated. Data collection ends on December 31st 2021. The process evaluation will start in March 2021. All patients whose COVID-19 disease have been cured will be invited to participate in an interview and in the questionnaire survey after the final consultation. Patients willing to participate in the process evaluation will be contacted by the study team via telephone to get more information about the study, answer open questions and schedule an interview and send the questionnaire to the patient. Interviews will take place in a timely manner after the patient provided his/her written informed consent. Evaluation, data analysis and publication are planned to be conducted continuously. If the COVID-19 pandemic persists or becomes active again the study may be prolonged after positive verification of an amendment to the ethics committee. In this case the practices have to reactivate the software with a new key after re-registration.

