### Sample size

The sample size of this observational study cannot be determined as it depends on the incidence of COVID-19 in the population and the further spread of SARS-CoV-2 is uncertain.

Currently, approx. 700 general practices use the CareCockpit software in Baden-Wurttemberg. It is expected that more practices will use the CareCockpit in the coming months. The maximum is limited by the number of practices who provide a trained VERAH. This number is presumed to be 2.000 practices. We expect participation in the CovidCare Study to be above 10 % of the existing 700 practices.

The sample for the qualitative study within the process evaluation is planned to reach saturation of data; a total of *n* = 20 (15–25) GPs and/ or VERAHs and *n* = 20 (15–25) patients is expected to be sufficient. The sample for the quantitative questionnaire survey comprises of all participating health care personnel and patients.

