For participation in the questionnaire survey, eligible GPs and VERAHs will be provided with a study information, informed consent forms and paper-based questionnaires. Interested persons will send the filled-in questionnaire and signed consent form in an enclosed post-paid envelope to the study central office.

As for patients, all participating patients will be informed about participation in an interview and in the questionnaire survey by the VERAH after the final consultation. The VERAH will send an expression of interest form and a post-paid envelope to the patients interested in participating in an interview and/or the questionnaire survey. The patient sends the expression of interest forms to the study central office using the enclosed post-paid envelope and will then be contacted by the study team via telephone to get more information about the study, answer open questions and schedule an interview. The study team will send the informed consent forms for the interview and the questionnaire respectively (each in duplicate), the study information and one post-paid envelope to the patient who will sign and return all informed consent forms to the study central office for study participation. A member of the study team will then sign all informed consent forms and return one copy (of the informed consent) to the patient and send him/her the questionnaire via post.

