#### Adverse event reporting and harms

No risks are anticipated for patients and general practices by participating in this study. However, we are in constant contact with all study sites to ensure that the CovidCare-Module can be used as intended and to early identify and solve occurring problems. All study sites are encouraged to report any difficulty to the study team. Moreover, we will explicitly explore problems and adverse events as part of the process evaluation, namely the interviews with the GPs, VERAHs and patients and report them in corresponding publications. Patients and general practices participating in this study can withdraw their consent at any time without indication of reasons. If the VERAH stops working at a general practice and there is no longer any VERAH employed, the GP-practice cannot participate in the CovidCare study any longer. New insights and findings of other studies that make the conduct of this study dispensable will lead to study termination.

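### The timeline invites cured patients to the interview and survey, while recruitment, sample size and eligibility set no cure condition; a practice following the timeline may miss patients who were hospitalised or are still ill

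*Protocol article*

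**What the plan says.** Four sections of the protocol article bear on which patients enter the process evaluation.

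- **Participant timeline:** "All patients whose COVID-19 disease have been cured will be invited to participate in an interview and in the questionnaire survey". The invitation follows the final consultation.
- **Recruitment and Implementation:** "all participating patients will be informed about participation in an interview and in the questionnaire survey by the VERAH after the final consultation". The instruments and the time point are the same, and there is no condition on cure.
- **Sample size:** "The sample for the quantitative questionnaire survey comprises of all participating health care personnel and patients". This covers the survey only. For the interviews, about 20 patients (15–25) are expected, justified by saturation.
- **Eligibility criteria and informed consent:** "Participants for the process evaluation have to participate in the CovidCare study as either patient or health care provider". Age of at least 18, German language skills and capacity to consent are also required, and then: "No further exclusion criteria have been defined".

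The Intervention description gives cured a definite meaning. It is the first of four reasons for ending the telephone monitoring: "the patient is cured (defined as alive and without symptoms of COVID-19 for 48 h and longer), (b) the patient is hospitalised". The third is death. The fourth is that "none of the above has happened not later than three weeks after first symptoms showed".

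Table 1 assigns patients' quality of life, perception of care, coping and satisfaction to the survey and interviews, together with the database. On harms, the protocol states that "we will explicitly explore problems and adverse events as part of the process evaluation", and names interviews with GPs, VERAHs and patients for this.

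**The concern.** Who is invited is a single rule, and the article gives two versions of it. One depends on how the illness went; the other does not.

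If practices apply the timeline version, the patient sample is selected on outcome. Being cured at closing is plausibly related to satisfaction, coping, perceived quality of care and the problems a patient would report, so the descriptive results could look more favourable than the experience of all participants. The groups at risk of being missed matter here: hospitalisation due to COVID-19 is the primary outcome, and patients still ill at three weeks have had a long course.

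Two features of the design add to this. The questionnaires are to be developed from the interview findings, so an experience absent from some 20 patient interviews may also be absent from the questionnaire. And the VERAH in each practice makes the approach, so with conflicting text different practices may invite different groups, leaving the denominator for the response rate unclear.

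**Working it through.** The protocol states no figure for this point, so the check compares the sections directly.

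**Step 1: does each section impose a cure condition?**

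| Section | Applies to | Cure condition |
|---|---|---|
| Participant timeline | interview and survey | yes |
| Recruitment and Implementation | interview and survey | no |
| Sample size | survey | no |
| Eligibility criteria | process evaluation as a whole | no; further exclusions expressly ruled out |

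One section stands against three.

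**Step 2: who falls between the two versions?** Take the four reasons for ending monitoring in turn, for a patient able to consent.

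| Reason monitoring ended | Timeline version | Other three sections |
|---|---|---|
| Cured | invited | invited |
| Hospitalised | not invited unless later counted as cured | invited |
| Deceased | not possible | not possible |
| None of these by three weeks | not invited unless later counted as cured | invited |

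The contradiction therefore affects living patients in the second and fourth rows. Patients who cannot consent are outside the process evaluation under either version, because the eligibility section excludes them.

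**Step 3: can the size be calculated?** Let *p* be the share of potential respondents left out and *d* the difference in mean response (or in proportion satisfied) between cured and not-cured patients. The cured-only result differs from the all-patient result by

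mean(cured) − [(1 − *p*) × mean(cured) + *p* × mean(not cured)] = *p* × *d*.

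The documents give neither *p* nor *d*: there is no expected hospitalisation rate, no expected share with symptoms at three weeks, and no anticipated satisfaction level. The direction is plausible and the size is unknown. For the interview strand the formula does not apply at all, since interviews run to saturation estimate no proportion; there the loss is one of content.

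**The case against.** The strongest reply is that the plan, read as a whole, does not restrict the process evaluation to cured patients. Eligibility, recruitment procedure and survey sample all point the other way, and the outlier is one sentence in a timeline section that does not contain the word only. That is a good reason to think the wider frame is intended. It does not remove the conflict, because naming the cured as the invited group restricts the invitation on a natural reading, and cured is a defined term in this protocol.

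Three stronger readings are tempting, and the documents do not support them.

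- *That patients who are not cured are never invited.* The definition of cured serves to say when telephone monitoring stops. The timeline does not say that cure must be reached by then. A hospitalised or slowly recovering patient may later count as cured, and the closing contact collects information on hospitalisation and ventilation, so such patients may well have a contact from which an invitation could follow. Exclusion is possible, not certain.
- *That problems are sought only among patients for whom the tool worked.* The harms section also names interviews with GPs and VERAHs, constant contact with the sites, and encouragement to report any difficulty. Staff can speak about hospitalised or still symptomatic patients. Nor does cure show that the tool worked: it is meant to detect severe courses early, so an admission may be the tool doing its job. What staff cannot replace is the patient's own account.
- *That the survey will be biased by some number of percentage points.* Any such number would be an assumed share multiplied by an assumed gap.

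It also stands that the process evaluation is descriptive and explorative, and that the primary and clinical secondary outcomes come from the CovidCare module and do not depend on who is invited.

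**Conclusion.** The inconsistency is real and lies in the current text: the timeline sets a cure condition that the recruitment, sample size and eligibility sections do not. Followed as written, it may leave out living, consenting patients who were hospitalised or are still symptomatic at closing, and with them their own reports on satisfaction, coping, perceived care and problems. Staff interviews fill part of the gap for problems.

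The conclusion rests on two readings: that the timeline sentence restricts the invitation although it lacks the word only, and that cured carries the meaning given in the intervention description. That the results would look too favourable rests on a further assumption, that cured patients respond more positively.

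The point is moderate to minor in weight. It concerns the process evaluation only and does not touch the analysis of hospitalisation. It is still more than a matter of wording, because the sentence decides whom practices approach.

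**What to change.** Align the Participant timeline with the eligibility, recruitment and sample size sections: invite every participating patient who is alive and able to consent, regardless of how monitoring ended. Where a patient cannot yet respond at closing, send the invitation later.

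Include a question in the patient questionnaire on course of disease (hospitalised, still symptomatic, recovered), so that results can be described by it. Using the reason for end of treatment held in the module would require linking questionnaires to module records. The article describes no such link, and states that the evaluating institution receives pseudonymised module data that it cannot trace to a person. A self-reported item avoids this, and the questionnaire is still to be developed.

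If the cured-only frame is what the investigators intend, the recruitment and sample size sections should be changed to say so, the eligibility section should carry the condition, and the restriction should be reported as a limit on the patient-reported findings.

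The cost is one revised sentence, some additional mailing, one questionnaire item and a submission to the ethics committees, since the amendment section requires this for changes affecting the study sample. The self-developed questionnaires are already due to go to the ethics committee as an amendment, so the change could be submitted with them if the timing allows.

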### Sample size

The sample size of this observational study cannot be determined as it depends on the incidence of COVID-19 in the population and the further spread of SARS-CoV-2 is uncertain.

Currently, approx. 700 general practices use the CareCockpit software in Baden-Wurttemberg. It is expected that more practices will use the CareCockpit in the coming months. The maximum is limited by the number of practices who provide a trained VERAH. This number is presumed to be 2.000 practices. We expect participation in the CovidCare Study to be above 10 % of the existing 700 practices.

The sample for the qualitative study within the process evaluation is planned to reach saturation of data; a total of *n* = 20 (15–25) GPs and/ or VERAHs and *n* = 20 (15–25) patients is expected to be sufficient. The sample for the quantitative questionnaire survey comprises of all participating health care personnel and patients.

### Sequence generation

Not applicable as this is not a randomized controlled trial.

### Recruitment {15} and Implementation

General practices are study sites and will check the inclusion criteria for all confirmed and suspected COVID-19 patients who they have included in the CovidCare-module during a phone call. The general practice then provides the patient/ legal representative with the study information and informed consent form via post or family members/ other persons supporting the patient in their quarantine.

 The patient/legal representative signs the informed consent form after being informed by the general practice via telephone. The signed informed consent form is transferred back via post or family members/ other persons supporting the patient in their quarantine.

If patients are in a temporary state of not being able to give their informed consent, for example due to invasive ventilation, a legal representative will be able to sign the informed consent and informed consent by the patient will be obtained once this temporary state is over.

 The general practice documents that they have sent the informed consent documents to the patients as well as that they have received the signed informed consent form in the CovidCare-module in the CareCockpit software. No data is transferred from the CovidCare-module if informed consent was not received by the practice and if the corresponding box in the software is not ticked.

The only additional time expenditure for patients concerns the informed consent.

For participation in the process evaluation, all participating GPs and VERAHs in the CovidCare study will be invited by an official letter from the study central office and will be asked to participate in an interview or the questionnaire survey, respectively.

For participation in an interview, eligible GPs and VERAHs will receive a response coupon with which they can declare their interest in participating in an interview. They will e-mail, fax or mail (using an enclosed post-paid envelope) the response coupon to the study central office. An employee of the study central office will call all interested participants in order to give further information on study participation, answer any open questions and arrange interview appointments. They will then be provided with a study information and the written consent form. The participant sends the signed informed consent sheets to the study central office using an enclosed post-paid envelope. The interviewer signs the form as well and sends back a copy to the participant.

For participation in the questionnaire survey, eligible GPs and VERAHs will be provided with a study information, informed consent forms and paper-based questionnaires. Interested persons will send the filled-in questionnaire and signed consent form in an enclosed post-paid envelope to the study central office.

As for patients, all participating patients will be informed about participation in an interview and in the questionnaire survey by the VERAH after the final consultation. The VERAH will send an expression of interest form and a post-paid envelope to the patients interested in participating in an interview and/or the questionnaire survey. The patient sends the expression of interest forms to the study central office using the enclosed post-paid envelope and will then be contacted by the study team via telephone to get more information about the study, answer open questions and schedule an interview. The study team will send the informed consent forms for the interview and the questionnaire respectively (each in duplicate), the study information and one post-paid envelope to the patient who will sign and return all informed consent forms to the study central office for study participation. A member of the study team will then sign all informed consent forms and return one copy (of the informed consent) to the patient and send him/her the questionnaire via post.

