### Outcomes

The primary outcome is hospitalisation due to COVID-19. The following indicators have been identified as secondary outcomes:

Diagnosis of pneumonia in confirmed and suspected COVID-19 patients [14].Utilisation of palliative care by confirmed and suspected COVID-19 patients during quarantine or stay at hospital.Mortality rate of confirmed and suspected COVID-19 patients (death at home, death in hospital, death in long-term care institution).Anxiety in confirmed and suspected COVID-19 patients using the Generalized Anxiety Disorder Index (GAD-2) [15].Identification of predictive risk factors for the outcomes such as hospitalisation, intensive care and mortality.

For the process evaluation we chose an exploratory sequential design. The process evaluation consists of a qualitative strand and a quantitative strand.

Overall, for the process evaluation we use the RE-AIM framework according to Glasgow and colleagues [16] to assess reach, efficacy, adoption, implementation and maintenance of the CovidCare surveillance and care tool. Table 1 provides an overview of the outcomes, indicators and methods/instruments of the process evaluation according to the RE-AIM framework.

**Table 1 Tab1:** Concept of the process evaluation

Outcomes	Indicators (examples)	Methods/Instruments
1) Reach The extent to which patients are reached by the implementation of CovidCare as well as the number of patients who are willing or refused to participate in CovidCare.	• How have patients been approached • Number of patients approached • Number of patients willing to participate in CovidCare • Patients: Reasons for refusal and drop-out, exclusion rate • Number of contacts per patient (i.e. telephone monitoring, particularly in the critical phase as defined by the RKI as a proxy whether GPs treat their patients according to guidelines) • Characteristics of participating patients	S, I, DB
2) Efficacy The efficacy of the CovidCare-module includes positive and negative impacts/effects for patients and HCP as well as the patients’ quality of life and the patients and the HCP’s satisfaction with the intervention.	• Positive and negative effects on patients’ quality of life, perception of (quality of) care, disease coping • Effects on health care personnel in managing Covid-19 patients • Satisfaction of HCP and patients with CovidCare • Comparison with patients with Covid-19/suspected cases but WITHOUT additional risk factors or aged >50	S, I, DB

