3) Adoption Adoption refers to the number of HCP and practices who agree to use the CovidCare-module and aims to understand the reasons for (not) participating in the intervention.	• Reasons for (not) participating in CovidCare; comparing characteristics of participants and non-participants (HCP, practices and patients) • Characteristics of participating HCP and practices • Barriers and facilitators	I, S, DB
4) Implementation Implementation refers to the extent to which CovidCare is used delivered as intended.	• Problems, time, and cost of the intervention • Adaptions that were necessary to implement/use CovidCare in daily practice	I, S, DB
5) Maintenance The extent to which the CovidCare-module became part of the daily practice routines of the individual HCP and the GP’s practice.	• Factors that facilitate the uptake of the intervention/ implementation into routine care • Suggestions for improving the intervention in order to enable CovidCare to become part of organizational practice	I

*DB* database, *HCP* health care personnel, *I* interviews, *S* survey

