#### Data management, Confidentiality

The evaluating institution (Department of General Practice and Health Services Research, University Hospital of Heidelberg) receives pseudonymized data only and cannot assign data to individuals.

Data collected in the CovidCare-module are secured in the general practices.

Pseudonymized data from patients who have given their informed consent is transferred to the study central office weekly. Data include all pseudonymized data collected in the initial assessment and the telephone monitoring as described in the intervention description.

Patients in each general practice are given a sequential number, which is linked to the corresponding general practice in the data. For the purpose of the identification of general practices, they export their unique license key as well as their practice identification number. In the study central office, a list linking the license key and the BSNR to a practice name and address data is stored separately and secured.

Data will be transferred via a secure unidirectional way (Zentraler Daten-Austausch-Container/ Kryptographie- und Transfer-Modul, ZeDaC-KTM). The ZeDaC-KTM interface allows for flexible, universal, and secure data exchange between health care organisations and their partners (here: Dept. of General Practice and Health Services Research). Hybrid encryption is used, which combines the benefits of asymmetric (public-key cryptosystem RSA (4096 bit)) and symmetric encryption (Advanced Encryption Standard (AES) 256 bit). The key length lies above the recommendations of the Federal Office for Information Security. This means that data that is temporarily stored on the ZeDaC-KTM server for the purpose of data transfer is encrypted and not readable. Only when data is collected from the server by the study central office, the encryption is reversed.

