#### Methods in analysis to handle protocol non-adherence and any statistical methods to handle missing data

The protocol non-adherence is limited to non-response, especially loss-to-follow-up. If necessary, a non-responder analysis will be performed. The data-sets themselves will obtain no missings due to mandatory fields. Therefore no imputation techniques will be needed.

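### Patients who die before they or a representative sign consent never enter the study data, so mortality is conditional on survival to consent, and patients who do not consent have no direct source in the planned comparison

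*Protocol article*

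**What the plan says.** **Export rule.** Recruitment {15} and Implementation states: "No data is transferred from the CovidCare-module if informed consent was not received by the practice". That sentence adds a second condition, an unticked box in the software, but the section Data management, Confidentiality settles the meaning: "Pseudonymized data from patients who have given their informed consent is transferred to the study central office weekly".

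**Consent route.** Patients are informed by telephone and sign on paper. "The signed informed consent form is transferred back via post or family members/ other persons supporting the patient in their quarantine". No delay is stated. During temporary incapacity, "for example due to invasive ventilation, a legal representative will be able to sign the informed consent", and the patient's own consent follows later. The eligibility section also allows representative consent for patients who cannot consent. Neither section mentions a patient who dies before anyone has signed.

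**Clock and outcome.** The Intervention description sets day 1 at the disease onset fixed by the GP and places the closing contact within three weeks of onset. Outcomes lists mortality of confirmed and suspected cases, at home, in hospital or in long-term care, as a secondary outcome. The statistical section offers a frailty model as one option for mortality. The consent date is among the items collected.

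**Process evaluation.** Table 1 lists "Number of patients approached" and refusals under Reach. Under Adoption it plans "comparing characteristics of participants and non-participants (HCP, practices and patients". Both rows name survey, interview and database as sources. The eligibility section restricts process-evaluation participants to people already in the CovidCare study.

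**The concern.** Entry into the dataset requires a signature obtained some time after the clock has started, in an illness that the protocol itself describes as changing within a few days. A patient can only be observed if he or she, or a representative, got as far as signing. For death, the interval from onset to consent is therefore survival-conditioned (immortal time).

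Two things are at stake. The mortality proportion would describe people who lived long enough for consent, not the outpatients the outcome names. And because the study's aim is the effect of risk factors, a factor that brings death forward would lose more of its deaths and look weaker than it is.

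The same rule leaves the exported database without patients who refused or never returned the form, which are the people needed to judge how selected the cohort is.

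**Working it through.** The protocol gives no mortality rate, consent delay or sample size, so there is no figure to reproduce. The mechanism follows from the text. Its size rests on assumptions only.

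**1. Mortality proportion.** Let M be true mortality and q the share of deaths that occur before anyone signs. Assume everyone else is equally likely to consent, so that this share cancels. Then

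observed mortality = M(1 − q) / (1 − Mq).

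With M = 3% (assumed):
- q = 10%: 0.0270 / 0.9970 = 2.71%
- q = 25%: 0.0225 / 0.9925 = 2.27%
- q = 40%: 0.0180 / 0.9880 = 1.82%

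Over M = 2%, 5% and 10%, the relative understatement is about 9–10% for q = 10%, 28–30% for q = 30% and 47–50% for q = 50%. It depends almost entirely on q.

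**2. What q might be.** Take a constant hazard over the 21 days of follow-up and a delay of d days from onset to signature: λ = −ln(1 − M)/21 and q = (1 − e^(−λd))/M. For M between 2% and 10%:
- d = 3: q about 14–15%
- d = 7: q about 34%
- d = 10: q about 48–49%

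The constant hazard is a convenience. If deaths cluster late in the course, q is smaller.

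**3. Risk-factor effect.** Take a true risk ratio of 2.0 (10% versus 5%) and apply the formula in each group:
- 30% lost in both groups: 7.22% / 3.55% = 2.03
- 30% lost in the high-risk group, 10% in the other: 7.22% / 4.52% = 1.60
- 50% versus 10%: 5.26% / 4.52% = 1.16

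Equal loss leaves the ratio almost unchanged. Distortion needs differential loss.

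**4. Non-participating patients, source by source.**
- Exported database: consenters only.
- Survey and interview of patients: study participants only.
- Survey and interview of practice staff: possible, and practices record in the module that forms were sent and received. This can supply counts, and second-hand information on patients who did not consent.

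So approached and refused counts can come from practice reports but not from the exported database. Characteristics of patients who did not consent have no direct source.

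**The case against.** Several stronger readings are tempting, and the text does not support them.

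- *Every death before the form arrives is lost.* No. Export depends on the practice receiving the form, not on the patient being alive at that moment. A form signed before death can still arrive and be exported. Only deaths before any signature are lost. Proxy consent narrows this further, since "a legal representative will be able to sign the informed consent" for a patient on ventilation.
- *The Reach counts cannot be produced.* Too strong. Table 1 assigns its sources to whole rows, and practices can report counts from their own module records. Contacts per patient and participant characteristics come from the export, and the staff and practice parts of the Adoption comparison do not depend on patient consent.
- *The missing-data section promises an analysis of non-consenters.* "If necessary, a non-responder analysis will be performed" follows a sentence about loss to follow-up and is most naturally read as concerning enrolled patients, whose data are exported. It does not conflict with the export rule.
- *The primary outcome suffers the same immortal time.* It does not. Admitted patients or their representatives can consent, and their earlier records are then exported. What remains is possible selection, in a direction the documents do not settle. Simply dropping patients who consented after admission would be a poor remedy: without delayed entry it makes onset-to-consent event-free for hospitalisation.

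Two fair objections go to the core. First, time origin and entry conditions are details an article may leave to an analysis plan. That stands as far as the model goes, so the missing delayed entry is not itself charged as an omission. But the consent rule and the absence of a route for early deaths are fixed in the protocol, and no later analysis can recover records that were never exported. Second, consent-gated export is an ethical constraint in an exploratory study. That stands too; the request is to account for its consequence, not to lift it.

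**Conclusion.** The point holds in limited form. Deaths before signature by the patient or a representative are excluded by design, so the mortality proportion is conditional on survival to consent. This mechanism, taken alone, biases it downward. Risk-factor effects on death are distorted only if early loss differs by risk group. The magnitude cannot be determined from the protocol: 3% appearing as 2.7% to 1.8%, and a risk ratio of 2.0 falling to 1.60 or 1.16, are illustrations on assumed inputs, and they take consent among all other patients as unrelated to outcome.

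Separately, the patient part of the non-participant comparison has no direct source, and the approached and refused counts depend on practice reports. A reader might infer that the hospitalisation result is biased in a known direction or that Reach cannot be assessed at all. Neither follows. This is worth correcting, but it does not undermine the study.

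**What to change.** 1. **Mortality.** In the time-to-death model, use delayed entry (left truncation) at the informed-consent date, and state that this date is the date of signature. Describe the raw mortality proportion as conditional on survival to consent, since delayed entry does not repair it. Delayed entry also assumes that the timing of consent is unrelated to the hazard of death given the covariates, which is doubtful where a representative signs because the patient has deteriorated. Say so. No new data are needed.

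2. **Hospitalisation.** Report how many patients consented after admission. Add a sensitivity analysis that counts only admissions after consent, with time at risk starting at consent. Do not merely exclude the patients who consented late.

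3. **Selection.** Have practices report aggregate, non-identifying counts from the module: eligible, forms sent, forms returned, died or admitted before consent. Suppress small cells, because single-practice counts may identify a patient. If this is not approved, remove the database as a source for the approached/refused and patient non-participant indicators in Table 1, and state that selection cannot be assessed.

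The cost is a small software or survey report and an ethics amendment. The protocol's section on amendments requires submission to and approval by two ethics committees, so a mere notification would not be enough. Items 1 and 2 need only analysis time.
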